To support these observations and establish more reliable data regarding the behaviour of SRC tumours, at the start of 2010 our team launched a French retrospective multicenter study of all consecutive oesophagogastric adenocarcinomas in 19 centres in France treated between January 1997 and January 2010 (ADCI001) [8]. Amongst 3010 patients registered 1050 (34.9%) had a SRC tumour, with 126 being metastatic at diagnosis and excluded from the study. The remaining 924 patients underwent an intention to treat analysis according to whether they underwent primary surgery (n = 753, 81.5%) or neoadjuvant chemotherapy (n = 171, 18.5%). Multivariate analysis showed pre-operative chemotherapy to be an independent predictor of poor survival (HR = 1.4, 95% CI 1.1-1.9, p = 0.042), with overall survival at 2 years of 27.1% in the primary surgery group versus 12.3% in patients treated with neoadjuvant chemotherapy. Hence, increasingly data is suggestive of SRC chemo resistance, and a deleterious effect of delaying definitive surgery for an ineffective treatment whose toxicity may cause host immunosuppression facilitating disease progression.

There is therefore clear impetus for a prospective randomised study to evaluate the appropriate perioperative therapeutic strategy for SRCs.

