## Methods/design

### Protocol overview

PRODIGE-19-FFCD1103-ADCI002 is a prospective multicentre controlled randomised phase II/III trial comparing current standard of care (2x3 cycles of perioperative Epirubicin, cisplatin, 5-fluorouracil (ECF) chemotherapy) with a strategy of primary surgery followed by adjuvant ECF chemotherapy (6 cycles) in patients with a SRC tumour and eligible for curative surgery. In phase II patients will be randomised using minimisation with stratification criteria – centre, tumour stage, performance status and tumour localisation. The principal objective will be to determine if the experimental arm (primary surgery followed by adjuvant chemotherapy) has a sufficient interest in terms of percentage of living patients at 24 months to be evaluated in a phase III trial. If ≤10% of patients in the experimental arm is alive at 24 months, phase III will not be initiated. Recruitment will be postponed for a 6 month period after the completion of phase II of the study to allow for the interim analysis of data. The primary objective of phase III will be to demonstrate the superiority of the experimental arm in terms of overall survival. The study is planned for a total duration of 10 years and is registered on clinicaltrial.gov website (NCT01717924).

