### Inclusion criteria

PRODIGE-19 will include patients with an adenocarcinoma of the stomach and Siewert type III tumours of the oesophago-gastric junction, with histological proof on pre-therapeutic biopsies of either a SRC tumour or diffuse type tumour according to the Lauren classification. Reliability of samples obtained from routine pre-treatment endoscopic biopsies to predict SRC histology has been recently demonstrated by our group [15].

All tumours of stage IB to III will be included (T1N+, T2N0 N+, T3N0 N+, T4N0 N+) as staged by routine endoscopic ultrasound examination (EUS), or by computerised tomography if the tumour is non-traversable at EUS. Patients will be between the ages of 18 and 80, must be assessed as suitable for curative surgery with the absence of visceral metastases or evidence of peritoneal carcinomatosis during a mandatory pretherapeutic staging laparoscopy. All included patients must have a weight loss of less ≤15% of body mass, have a World Health Organisation performance status of ≤2, with an ejection fraction of ≥50% prior to the administration of Epirubicin and must not have been previously treated with either chemotherapy or radiotherapy for a gastric cancer. Patients must have a neutrophil count of ≥1500/mm^3^, platelet count of ≥100,000/mm^3^, a creatinine clearance of >50ml/minute and a total Bilirubin <1.5 times the upper limit of normal. All patients must give their informed consent for participation in this trial.

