### Statistical evaluation and sample size calculation

Phase II– The phase II part of this trial will determine the percentage of patients in the experimental limb of the study (group B) who are alive at 24 months and thus validate the interest pursuing the evaluation of a strategy of primary surgery in a subsequent phase III trial. To demonstrate the interest of the experimental arm of this study, it will be necessary to include 40 in each treatment arm, with a unilateral alpha error of 5% and a power of 85%. Taking into account a 5% level of loss to follow-up, 84 patients will be included in total (42 in each treatment arm). If 7 or less patients are alive after 24 months, then the treatment B will be considered not interesting. Survival data for patients from phase II of this trial will allow for the readjustment of the number of patients required to be enrolled in the phase III trial according to the adaptive trial design.

Phase III – The objective of the phase III trial will be to demonstrate the superiority of group B and the principal outcome criteria will be overall survival. To demonstrate a desired 10% difference in overall survival in favour of group B at 24 months, with a bilateral alpha error of 5% and a power of 85%, it will be necessary to observe 291 deaths. With an estimated rate of inclusion of 6 patients per month, with a 5% rate of loss to follow-up and surveillance of the last included patient of 24 months, a total of 314 patients will have to be recruited. On this basis 230 additional patients will need to be recruited after the completion of phase II.

Two intermediate analyses are planned, one for Phase III sample size read justement and the second one to allow for the early identification of the superiority of group B. The first intermediate analysis of survival data will take place at the end of phase II. The second intermediate analysis will be performed after either 175 deaths or 60% of events have occurred.

Statistical analysis for phase II will be performed on a modified intention to treat population meaning all patients who can be evaluated and who are not lost to follow up at 24 months. For phase III, analysis of the main criteria will be performed on an intention to treat (ITT) principle. The per-protocol population will be defined as the ITT population having no major deviation or major of the protocol.

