Recently Messager et al [8] have published the results of a large multicentre comparative cohort study investigating the impact of peri-operative chemotherapy on survival in patients with SRC gastric tumours. It represents the largest study conducted on this histological subtype and involved analysis of 1050 patients diagnosed with SRC gastric tumours. No survival benefit was demonstrated for patients with SRC histology receiving peri-operative chemotherapy. Nor did neoadjuvant therapy result in tumour down-staging, down-staging of nodal disease, or decrease the disease recurrence. Indeed the authors found some evidence that disease progression during neoadjuvant treatment may have occurred in this subgroup of patients - extended resections were more commonly required and a longer median survival for patients treated with surgery alone prior to the incorporation of peri-oerative chemotherapy into the French guidelines for GA in 2006. This provides a clear imperative of the assessment of an alternative treatment strategy.

As several studies [11-14] have suggested a relative chemo resistance for SRC tumours and delay in definitive surgery may favour tumour progression [8] we hypothesise that a policy of primary surgery for SRC tumours, followed by adjuvant chemotherapy, will improve overall survival at 2 years when compared to a standard peri-operative chemotherapeutic strategy. This primary outcome criteria is justified as it provides a short term evaluation criteria (important in view of the very poor prognosis associated with this disease) and survival at 24 months has been found in a multicentre retrospective series of over 1000 patients to be significantly different (27% vs. 10%) [8].

This randomised trial will provide high level evidence regarding the value of a strategy of primary surgery for SRC gastric tumours. Whilst the development of new biomarkers and associated targeted therapies are awaited to individualise gastric cancer therapy, the results of this trial should will help further in devising individualised protocols of patient care in a tumour group whose diversity increasingly demands assessment of alternative strategies.

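### The phase II go/no-go count keeps its stated 5% error only if uninteresting 24-month survival is about 10%, a figure from a less selected historical cohort that the article elsewhere reports as 12.3%

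*Protocol article*

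**What the plan says.** Statistical evaluation and sample size calculation sets the size and error rates of phase II: "it will be necessary to include 40 in each treatment arm, with a unilateral alpha error of 5% and a power of 85" per cent. The rule follows: "If 7 or less patients are alive after 24 months, then the treatment B will be considered not interesting". That section names neither the uninteresting rate (p0) nor the target rate (p1). The Protocol overview words the same decision as a percentage: "If ≤10% of patients in the experimental arm is alive at 24 months, phase III will not be initiated".

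The Discussion gives a historical basis for 24-month survival: "survival at 24 months has been found in a multicentre retrospective series of over 1000 patients to be significantly different (27% vs. 10" per cent). The Background describes that series as a "French retrospective multicenter study of all consecutive oesophagogastric adenocarcinomas in 19 centres in France treated between January 1997 and January 2010". It says that 126 patients metastatic at diagnosis were excluded and 924 analysed. It gives the result as "overall survival at 2 years of 27.1% in the primary surgery group versus 12.3% in patients treated with neoadjuvant chemotherapy".

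Inclusion criteria restricts the trial to gastric and Siewert III tumours of stage IB-III and to ages 18-80. Performance status must be 2 or better and weight loss at most 15%, with cardiac, marrow, renal and liver limits. Patients must be fit for curative surgery, "with the absence of visceral metastases or evidence of peritoneal carcinomatosis during a mandatory pretherapeutic staging laparoscopy".

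**The concern.** A single-arm test against a historical rate is only as good as that rate. If p0 is too low for the patients who can enter, arm B can pass because of who was enrolled rather than because of the strategy, and the printed 5% describes a population other than the one under test.

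The 10% appears to come from a cohort with broader entry than the trial, and nothing in the article adjusts it. The article also gives two values for the same cohort arm. Arm A is randomised alongside, but the rule does not use it, so concurrent controls do not repair a wrong p0 at this decision.

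**Working it through.** **Inputs.** n = 40 evaluable in arm B, stop at 7 or fewer (go at 8 or more), one-sided 5%, power 85% (Statistical evaluation). Candidate p0: 10% (Protocol overview, Discussion) and 12.3% (Background). The values 20%, 30% and 40% are assumptions, since the article gives no 24-month survival for eligible patients.

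**Reproducing the plan.** With X ~ Binomial(40, p), P(go) = P(X ≥ 8).
- At p = 0.10, P(X ≥ 8) = 0.042 and P(X ≥ 7) = 0.0995, so 8 is the exact 5% cut-off for p0 = 10%.
- At p = 0.26, P(X ≥ 8) = 0.853.
- The smallest n with exact alpha ≤ 5% and power ≥ 85% for 10% vs 26% is 40, with go at 8 or more. For 25% it is 47 and for 27% it is 34.

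So p0 = 10% and p1 = 26% return the printed design. The error of the printed rule reaches 5% at a p0 of about 10.4%, which leaves almost no margin above 10%.

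**The same rule at other values of p0, and the cut-off that would restore 5%.** The cut-off is the smallest r with P(X ≥ r | p0) ≤ 0.05. The last column solves P(X ≥ r | p1) = 0.85.

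| p0 | False-go, printed rule | Printed rule stops | Go at r or more (exact error) | Arm B rate with 85% power |
|---|---|---|---|---|
| 10% | 4.2% | 95.8% | 8 (4.2%) | 26% |
| 12.3% | 11.1% | 88.9% | 10 (2.1%) | 31% |
| 20% (assumed) | 56% | 44% | 13 (4.3%) | 39% |
| 30% (assumed) | 94% | 5.5% | 18 (3.2%) | 52% |
| 40% (assumed) | 99.8% | 0.2% | 22 (3.9%) | 62% |

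At 12.3%, go at 9 or more has error 5.06%, so 10 is needed only by a hair.

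**Wording of the rule.** 7/40 = 17.5%, while 10% of 40 is 4. Read as an observed proportion, the Protocol overview sentence would mean stopping at 4 or fewer, and P(X ≥ 5 | 0.10) = 0.371. It probably names p0 rather than the observed cut-off, but it does not say so.

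**Phase III, secondary.** The article states a 10-point gain and 291 deaths but no base rate. For 10% vs 20%, HR = ln 0.20 / ln 0.10 = 0.699. Freedman's formula gives (1.960 + 1.036)² × [(1 + 0.699)/(1 − 0.699)]² ≈ 286 deaths, within 2% of 291. For 12.3% vs 22.3% it gives 328, and for 20% vs 30% it gives 433. A base rate near 10% is therefore inferred from the fit.

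**The case against.** The case on the other side has real force.

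- **The cohort was not unselected.** Metastatic patients were removed, and the 924 analysed went to primary surgery or neoadjuvant chemotherapy. Only "less selected" is supportable, and fuller cohort criteria may stand in the cited source, which is not at hand.
- **Not every filter favours survival.** The trial also bars T1N0 tumours, which the cohort, as described, did not exclude. Some limits are loose: age to 80, performance status up to 2, T4 with nodes. The laparoscopy and fitness limits probably raise survival on balance, but by an unknown amount.
- **A reader might infer that the rule can hardly ever stop the trial.** That is true only from about 30% upwards. At 12.3% the rule stops 89% of the time and at 20% it stops 44%. No survival figure for signet ring tumours in the article reaches 30%. The 5-year rates of 36-38% with perioperative chemotherapy cover all histologies, and the article says signet ring tumours do worse, so they indicate direction at most.
- **A reader might count as a fault that the rule passes 89% of the time at 27.1%.** It is the designed power near the hoped-for rate. A null below the target is normal.
- **A reader might infer that the same rate fixes the phase III death target.** The base rate there is not stated, and the plan already provides for readjusting phase III numbers from phase II survival, where arm A gives control survival in eligible patients.
- **A lenient rule costs efficiency, not phase III validity.** Superiority is still tested at two-sided 5%.

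What remains is that arm B is read alone against a fixed count, and the 5% attached to that count fails at the article's own 12.3% and at any higher p0. The planned readjustment, as described, resizes phase III and does not revise this count.

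**Conclusion.** The concern holds in a limited form. The printed 5% is correct for p0 = 10% and, to rounding, nowhere above it. At the 12.3% given in the Background for the same cohort arm, the error is 11.1%, more than double the stated level, before any difference in patient selection is considered. Above that the size is conditional: 56%, 94% and 99.8% at assumed nulls of 20%, 30% and 40%.

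This rests on two inferences. The first is that p0 is 10%, which the exact reproduction of n = 40 and the cut-off supports. The second is that this 10% is the cohort figure in the Discussion, since the statistical section names no source. The documents do not show that arm B would pass on selection alone, nor what eligible patients' survival is. The 291-death target appears to share the 10% base but can be corrected by the planned readjustment, so it is a secondary point.

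**What to change.** Before any phase II outcome is read:

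1. Reconcile the 10% in the Discussion with the 12.3% in the Background.
2. Re-estimate 24-month survival in cohort patients who meet the inclusion and exclusion criteria, as far as the cohort recorded them. Use pre-treatment information only. Selecting on absence of carcinomatosis at surgery would remove patients who progressed during neoadjuvant chemotherapy and bias p0 upward.
3. State that rate as p0. Restate the stop count as its exact 5% cut-off for 40 patients: go at 10 or more for 12.3%, 13 or more for 20%, 18 or more for 30%. State the arm B rate that then has 85% power (31%, 39% and 52% respectively).
4. Make the percentage wording in the Protocol overview agree with the count, saying whether it is p0 or an observed proportion.
5. At the planned readjustment, base the phase III control rate on arm A data and state it.

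The cost is a reanalysis and one amended paragraph, if the cohort holds the needed variables; the article does not say whether performance status or laparoscopy findings were recorded. The real price is a higher bar: with 40 patients, arm B must be truly better than the present 26% to have 85% power.

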### Endpoints of trial

The primary endpoint of this trial will be the evaluation of the percentage of patients still alive 24 months after randomisation. The secondary endpoints for this trial include, overall survival (OS) at 36 months, disease free survival (DFS) at 24 and 36 months, R0 resection rates, treatment tolerance, postoperative mortality and morbidity evaluated by Clavien-Dindo severity index [16], rates of completion of all elements of the planned therapy, the prognostic impact of positive peritoneal cytology and the assessment of quality of life (EORTC QLC-C30 and EORTC STO 22). A complementary study, subsequently described, will assess the emotional and cognitive impact of surgery and perioperative chemotherapy for both the patient and their partner.

OS is defined as the time interval between inclusion and death from whatever cause and patients lost to follow-up will be censured at the last date of follow-up. Disease free survival will be defined as the time interval between the date of inclusion and the date of first recurrence or the date of death in the absence of disease recurrence. The R0 resection rate will correspond to the percentage of patients benefitting from a micro and macroscopically complete resection [17]. Neoadjuvant and/or adjuvant treatment tolerance will be estimated according to the National Cancer Institute Toxicity Criteria (NCI-CTC version 4.0). Evaluation of the uptake of all elements of planned treatment will be performed and quality of life questionnaires and human and social sciences questionnaires will be completed at 4 defined time-points – randomisation, the eve of commencement of treatment, 1 month (+/−7 days) after leaving hospital following surgery and 1 month (+/−7 days) after completing adjuvant chemotherapy. The quality of life questionnaires will also be completed at each 4 monthly follow-up visit.

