Continuous variables will be described by their mean and standard deviation or median, Interquartile Interval (Q1-Q3) and range. Survival endpoints will be estimated using the Kaplan Meier method, described by median values with 95% confidence Interval and compared in Phase III using the log-rank test. QoL data will be analysed according to treatment arm and treatment tolerance assessed using the National Cancer Institute Toxicity Criteria – (NCI CTC). The Clavien-Dindo scale will be used to assess peri-operative complications [16]. Cox univariate and multivariate analyses will allow exploratory analyses of prognostic factors, time until deterioration of QoL and disease free survival.

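### The phase II go/no-go drops patients last seen alive before 24 months and applies a fixed count of 7 with no denominator, so its estimate and error rates shift with losses: modestly at the planned 5%, more beyond it

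*Protocol article*

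**What the plan says.** All of the phase II rule stands in the protocol article under Statistical evaluation and sample size calculation, except where noted.

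- Design: "it will be necessary to include 40 in each treatment arm, with a unilateral alpha error of 5% and a power of 85"%. The target survival rate behind that power is not stated.
- Inflation: "Taking into account a 5% level of loss to follow-up, 84 patients will be included in total (42 in each treatment arm").
- Decision: "If 7 or less patients are alive after 24 months, then the treatment B will be considered not interesting". No denominator is attached.
- Analysis set: a modified intention-to-treat population, explained as "all patients who can be evaluated and who are not lost to follow up at 24 months".
- Under Protocol overview the same decision appears as a percentage: "If ≤10% of patients in the experimental arm is alive at 24 months, phase III will not be initiated".
- Under Endpoints of trial, in the definition of overall survival, "patients lost to follow-up will be censured at the last date of follow-up" (that is, censored). The closing paragraph of the statistical section adds that "Survival endpoints will be estimated using the Kaplan Meier method".

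**The concern.** A patient who dies at month 6 has a known 24-month status and is evaluable. A patient last seen alive at month 6 is not. Membership of the analysis set therefore depends partly on the outcome. Because the decision is a bare count of survivors, removing a lost patient has the same effect on it as counting that patient dead.

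The cut-off of 7 fits 40 evaluable patients. The article does not say what applies if the number with known status is 38, 41 or 42, so the real alpha and power are those of whatever number happens to remain.

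The decision at stake is whether phase III opens. The article already contains a method that uses the lost patients' follow-up (censoring with Kaplan-Meier) but does not use it for this decision.

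**Working it through.** **Inputs.** From the article: 40 evaluable per arm, 42 enrolled per arm, 5% loss, one-sided alpha 5%, power 85%, go at 8 or more alive. The null rate p0 = 10% is taken from the percentage rule in the Protocol overview; the article does not label it as a null. The target p1 is not stated. I assume 26%, the value that reproduces the design. The nearest documented figure is 27.1%, the two-year survival of the primary-surgery group in the retrospective study described under Background.

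**1. The plan's own figure.** In a single-stage exact binomial design, alpha = P(X ≥ 8 | n = 40, p = 0.10) = 4.2% and power = P(X ≥ 8 | n = 40, p = 0.26) = 85.3%. With these rates, 40 patients and a go at 8 is the smallest design meeting 5% and 85%. Inflation: 40 × 1.05 = 42 per arm, 84 in total. The sample size reproduces.

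**2. Fixed count, varying number evaluable.** P(X ≥ 8) for m evaluable patients:

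| m | p = 10% (alpha) | p = 26% | p = 27.1% |
|---|---|---|---|
| 38 | 3.2% | 80.9% | 84.7% |
| 40 | 4.2% | 85.3% | 88.6% |
| 42 | 5.4% | 88.9% | 91.6% |

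If nobody is lost, alpha exceeds the stated 5%.

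**3. Bias from the analysis set.** Assume exponential death with rate λ = −ln(S)/24 per month and independent exponential loss with rate μ. Choose μ so that the share actually lost before death or month 24 is L = μ/(μ+λ) × [1 − exp(−24(μ+λ))]. The probability of being observed alive at 24 months is a = exp(−24(μ+λ)), and the evaluable-only proportion is a/(1 − L).

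- S = 26%, L = 5%: λ = 0.0561, μ = 0.0039, a = 0.2366; 0.2366/0.95 = 24.9%.
- S = 26%, L = 10%: μ = 0.0082, a = 0.2137; 0.2137/0.90 = 23.7%.

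The estimate is thus about 1.1 and 2.3 points low. Under this model the lost patients' true 24-month survival is (S − a)/L = (0.26 − 0.2366)/0.05 ≈ 47%, well above that of the patients who remain, which is why dropping them lowers the estimate.

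**4. Both effects together.** With 42 enrolled, P(go) = P(X ≥ 8 | n = 42, p = a):

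| Actually lost | True 10% | True 26% | True 27.1% |
|---|---|---|---|
| 0% | 5.4% | 88.9% | 91.6% |
| 5% | 2.7% | 81.0% | 84.9% |
| 10% | 1.2% | 70.1% | 75.2% |

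**5. Kaplan-Meier on all 42, losses censored.** Simulation under the same model (200,000 trials per cell) gives mean estimates of 10.0%, 26.0% and 27.1% at those true rates, at every loss level. Probability of a go by threshold:

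| Actually lost | >17.5%, true 10% | ≥20%, true 10% | ≥20%, true 26% | ≥20%, true 27.1% |
|---|---|---|---|---|
| 0% | 5.4% | 2.1% | 80% | 84% |
| 5% | 7.1% | 2.9% | 80% | 84% |
| 10% | 8.2% | 3.7% | 79% | 83% |

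The value 17.5% is 7/40; 20% is 8/40.

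**The case against.** Much of the case on the other side stands. Enrolling 42 to obtain 40 is ordinary inflation, and the design reproduces. At the documented 27.1% and the planned 5% loss, the count rule gives 84.9% power with alpha 2.7%, in line with the stated 85% and 5%. A bias of 1.1 points is small beside a standard error of about 7 points. Losses of 10% appear nowhere in the article; they are a range, not a forecast. At planned loss, Kaplan-Meier with a 20% threshold does not beat the count (84.0% against 84.9% at 27.1%); its gain comes when losses exceed plan.

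Several stronger readings are tempting but not supported:

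- A reader might infer that the stated alpha and power fail as planned. They do not at 27.1%. At 26% the go probability is about 81%, but 26% is an assumption.
- A reader might infer that survival is necessarily underestimated. That needs non-informative loss. If lost patients fared worse than those remaining, the direction would reverse. Keeping the deaths is also an inference from the wording, although the natural one.
- A reader might see a flat contradiction with the overall survival definition. The primary endpoint is a binary 24-month status, and the censoring sentence defines a time-to-event endpoint. The two can coexist; the better method is simply not applied to the decision.
- A reader might infer that the phase III sample-size readjustment uses the reduced set. The article says only that phase II survival data will inform it.
- A reader might think it enough to compare Kaplan-Meier with 17.5%. That breaches the stated alpha.

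What counts as evaluable may be spelled out in the full protocol, so I do not treat its absence here as a defect.

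**Conclusion.** The point holds in limited form. The stated analysis set excludes patients in an outcome-dependent way, and the fixed count gives error rates that move with the number lost. Under independent exponential loss and an assumed true rate of 26%, the downward bias is about 1 point at 5% actually lost and 2 points at 10%, and the probability of a go falls from 89% with no loss to 81% and 70%. The error runs mainly toward wrongly abandoning the experimental arm; the exception is complete follow-up, where alpha is 5.4%. At planned loss the effect is modest and at 27.1% the stated power is kept. The sample size itself is not in error. These sizes rest on p0 = 10%, on the assumed target rate and on the loss model.

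Separately, 7 of 40 is 17.5%, which does not match the 10% rule in the Protocol overview. The two statements of the decision must be reconciled.

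**What to change.** - Define the phase II analysis set as all patients randomised to group B. Estimate 24-month survival by Kaplan-Meier with censoring at last contact, which the article already provides for survival endpoints.
- State p0 and the target rate. Calibrate the threshold so that one-sided alpha stays at or below 5% over a plausible range of losses. A threshold of 17.5% fails (about 5.4%, 7% and 8% at 0%, 5% and 10% lost). An illustrative threshold of at least 20% gives about 2% to 4%.
- Restate the power: for that illustration, about 80% at 26% and 84% at 27.1%.
- Use one decision rule throughout, reconciling the count with the 10% rule in the Protocol overview.
- Keep the complete-case count as a sensitivity analysis. If a count remains the rule, tabulate the cut-off by number with known status: go at 8 or more for 38 to 41, and at 9 or more when all 42 are evaluable (alpha 2.1%, power 80.0% at 26%). This holds nominal alpha but does not remove the bias.

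Cost: no extra patients or data, but the operating characteristics must be recalculated, and the stated power becomes slightly less favourable than 85%.

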### Randomisation

Randomisation will be performed by minimisation with stratification criteria – centre, tumour stage, performance status and tumour localisation. The maximum delay between randomisation and either the start of neoadjuvant treatment or surgery will be 4 weeks. A randomisation number and the treatment allocation are sent by facsimile communication by the “Centre de Randomisation-Gestion-Analyse” (CRGA) at the Fédération Francophone de Cancérologie Digestive (FFCD) headquarters in Dijon, France to the investigator after the receipt of the inclusion form.

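### The minimisation factors play no stated part in the phase III survival comparison; if the log-rank is run unstratified it is valid but conservative and forgoes power

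*Protocol article*

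**What the plan says.** On allocation, the Randomisation section states: "Randomisation will be performed by minimisation with stratification criteria – centre, tumour stage, performance status and tumour localisation". The Protocol overview lists the same four factors.

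On the phase III objective, the section on statistical evaluation and sample size sets out to "demonstrate the superiority of group B and the principal outcome criteria will be overall survival". The target is worded "To demonstrate a desired 10% difference in overall survival in favour of group B at 24 months", and the size follows: "with a bilateral alpha error of 5% and a power of 85%, it will be necessary to observe 291 deaths".

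On the test, the same section says survival endpoints are "described by median values with 95% confidence Interval and compared in Phase III using the log-rank test". Stratification and adjustment are not mentioned either way.

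On covariate models: "Cox univariate and multivariate analyses will allow exploratory analyses of prognostic factors". That sentence goes on to time to deterioration of quality of life and disease-free survival, so the Cox models are not confined to prognostic factors. They are still called exploratory, and the treatment comparison for overall survival is not among their listed uses.

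**The concern.** Minimisation makes the arms more alike on the chosen factors than chance would. If those factors affect survival, the treatment comparison varies less from trial to trial than under simple randomisation. The variance of an unstratified log-rank test does not take credit for this. The test then rejects too seldom under the null and is less sensitive than one that uses the factors.

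The factors are plausibly prognostic here. Eligibility runs from stage IB to III and up to WHO performance status 2.

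Wasted efficiency would be hard to recover. The plan needs 291 deaths from 314 patients (291/314 = 93%). After 5% loss about 298 patients remain (0.95 × 314), so there are few further deaths to wait for. The superiority look at 175 deaths (175/291 = 60%) would presumably use the same test.

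**Working it through.** **Step 1: the planned number of deaths.** From the article: two-sided 5%, power 85%, 10-point difference at 24 months, 291 deaths. The phase III calculation gives no control-arm survival. I assume 10% vs 20%, taking 10% from the Discussion. The Background gives a different figure for the same retrospective series: "overall survival at 2 years of 27.1% in the primary surgery group versus 12.3% in patients treated with neoadjuvant chemotherapy".

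- HR = ln(0.20)/ln(0.10) = 1.609/2.303 = 0.699.
- (z for 5% two-sided + z for 85%)² = (1.960 + 1.036)² = 8.98.
- Freedman: 8.98 × [(1 + 0.699)/(1 − 0.699)]² = 286 deaths. A 2% allowance for one interim look gives 291.7.
- Schoenfeld: 4 × 8.98/(ln 0.699)² = 280 deaths.
- Power at 291 deaths by Schoenfeld: 86.3%.

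So 291 is reproduced to within 2% under 10% vs 20%. Under 12.3% vs 22.3% the requirement would be 322 (Schoenfeld) or 328 (Freedman), which does not match. Both formulas describe an unadjusted test.

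**Step 2: simulation.** Taken from the article: 314 patients, the four minimisation factors, analysis at 291 deaths and, in Simulation 1, accrual of 6 per month. Assumed, because the article does not give them:

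- 20 centres and a minimisation coin biased at 80%;
- the prevalence of each factor level;
- hazard ratios per level for stage/performance status/location of 1.3/1.2/1.1 (weak), 1.6/1.4/1.15 (moderate) and 2.0/1.6/1.3 (strong).

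Simulation 1 used 1,500 runs per scenario, with no loss to follow-up and no interim look. Simulation 2 was a separate program with 2,000 runs and the same factor effects. The Monte Carlo standard error near 85% power is about 0.9 and 0.8 points respectively.

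Power (%), plain log-rank → Cox adjusted for stage, performance status and location:

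| Effect definition | Factors | Simulation 1 | Simulation 2 |
|---|---|---|---|
| HR 0.699 conditional on factors | none | 86.2 → 85.8 | 86 → 87 |
| | weak | 84.8 → 88.0 | 82 → 84 |
| | moderate | 76.1 → 84.6 | 75 → 83 |
| | strong | 66.4 → 81.1 | 65 → 80 |
| Marginal 10% vs 20% at 24 months | weak | 87.8 → 89.8 | 87 → 89 |
| | moderate | 89.0 → 94.1 | 89 → 93 |
| | strong | 93.9 → 98.8 | 91 → 97 |

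The gap is about 2–15 points under the conditional definition and about 2–6 under the marginal one. The upper figure of 15 is not a bound: an extreme set of 2.5/2.0/1.4, conditional, gave 52.1 → 78.9 in Simulation 1. Under the marginal definition the conditional hazard ratios consistent with 10% vs 20% are 0.682, 0.649 and 0.603. These are stronger than 0.699, which is why the plain test does not fall below 85%.

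Two-sided type I error in Simulation 2 (none/weak/moderate/strong):

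- plain: 4.9/4.0/3.4/2.1%;
- adjusted Cox: 5.3/5.1/4.5/4.0%.

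In Simulation 1 the one-sided error of the plain test was 1.1% under moderate and strong factors, against a nominal 2.5%.

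**Step 3: which way of using the factors is safe.** Change in power against the plain test:

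- Six strata of stage by performance status (Simulation 2, none/weak/moderate/strong): −1.5/0/+5/+12 points conditional and −2.5/0/+2.5/+5 marginal. With inert factors the two definitions coincide, so −1.5 and −2.5 estimate the same quantity.
- Strata of stage, performance status and location (Simulation 1): −10/−6/0/+7 conditional (none to strong) and −6/+1/+2 marginal (weak to strong).
- Strata of all four factors including centre (Simulation 1): power falls to 25–28% conditional and 28–45% marginal. With about 20 centres the strata are too sparse for most patients to contribute to the comparison.

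**The case against.** **The article never says the test is unstratified.** This stands. A condensed article may leave stratification to the full protocol or analysis plan, and neither is shown. A reader might infer that the trial has committed itself to a plain log-rank; the text does not establish that. The point survives because the article does more than stay silent. It names the confirmatory test without the factors and gives the covariate models an exploratory role.

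**The power loss is not a figure from the documents.** This also stands. The article gives no hazard ratios or prevalences for the factors in this population, so any single number reflects what was assumed.

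**The planned power is not missed.** A reader might infer that the trial falls short of its 85%. That would follow only if a hazard ratio near 0.70 held within levels of the factors. The article states its target as a difference in survival at 24 months, which reads naturally as a population-level effect, and 291 deaths fits an unadjusted test of it. A further check used three-factor minimisation, other assumed factor effects and marginal 10% vs 20%. It gave 88%, 92% and 93% for the plain test against 90%, 95% and 97% when stratified on stage and performance status. What is lost is extra power, not the promised power.

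**There is no validity problem.** Correct: the error is on the conservative side, so false-positive risk is not raised. Nor is an unadjusted hazard ratio closer to 1 a bias in itself. It estimates a marginal rather than a conditional effect, and the article's account of the survival comparison does not promise a hazard ratio.

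**The remedy can cost power.** True of fine stratification, as Step 3 shows, but not materially of the main-effects Cox model.

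**Conclusion.** The point holds conditionally. As the article stands, the factors that drive allocation have no stated role in the phase III primary comparison. If the log-rank is run unstratified, its two-sided type I error is about 2–4% rather than 5% when the factors are prognostic.

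The power forgone is about 2–6 points if the 10-point difference is marginal at an assumed 10% vs 20%, with the plain test still at or above 85%. It is about 2–15 points, across weak to strong factors, if a hazard ratio of about 0.70 is conditional. Both ranges rest on assumed factor effects, prevalences and number of centres. The direction is secure; the size is not. This is a matter of efficiency and clarity, and it does not show an underpowered or invalid trial.

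**What to change.** State before unblinding that the phase III primary comparison, and the superiority interim, account for tumour stage and performance status. Two forms are suitable:

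- a Cox model with main effects for stage, performance status and localisation; or
- a log-rank test stratified on stage and performance status only.

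Do not stratify on centre; handle it as a random or pooled effect. Keep the unstratified log-rank as a sensitivity analysis. If a full protocol or analysis plan already specifies this, confirming it there is enough.

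The cost is a sentence or two and routine code, since the factors are recorded at randomisation. The statistical downside is negligible for the adjusted Cox test (0.4 points in Simulation 1 with inert factors, within simulation error). For the six-stratum log-rank it is up to about 2.5 points if the factors turn out not to be prognostic.
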